## Abstract

Introduction: Acquired brain injury (ABI) constitutes a significant and growing global public health concern. People with ABI often face a range of physical and psychosocial challenges that span the domains of “body structure and function”, “activity”, and “participation”, as defined by the International Classification of Functioning, Disability, and Health. Multidisciplinary approaches based on exercise therapy with social leisure activities are essential to improve physical recovery and health-related quality of life after injury. Methods: Adults with ABI, aged > 18 years, in the subacute or chronic stage (within more than one month after the injury) will be recruited through a rehabilitation center. Adults will be randomized to receive either a racket sports-based exercise therapy program combined with usual care (sET) or usual care alone (UC) using a random number sequence with a 1:1 allocation ratio. sET intervention consists of an 8-week exercise therapy program focusing on different racket sports skills, 1 h in duration, 2 days/week. It will be delivered by a physiotherapist in tailored, face-to-face, group-based sessions. Primary outcomes will be the health-related quality of life (SF-36) and upper extremity motor function (Fugl-Meyer Assessment-Upper Extremity Scale). Discussion: The study proposes an intervention that combines sports-based exercise therapy with usual care. It aims to determine whether this intervention improves the health-related quality of life and upper limb motor function in adults with ABI compared with usual care alone. The results of this study may have clinical implications for the rehabilitation of this population.

## 1. Introduction

Acquired brain injury (ABI) constitutes a significant and growing global public health concern. ABI is a disorder of the mature brain, regardless of its severity or duration, resulting from various etiologies, including stroke, traumatic brain injury, tumors, or infectious diseases [1,2].

People with ABI often face a range of physical and psychosocial challenges, spanning all domains of the International Classification of Functioning, Disability and Health (ICF) model. They experience impairments in the area of “body structure and function” domain (e.g., spasticity, muscle weakness, or poor motor control). In addition, these impairments can have a ripple effect, limiting their abilities within the “activity” domain (e.g., difficulties with fine motor function) and also affecting the “participation” domain (e.g., reduced physical activity and participation in sport) [2]. These patients may experience a reduced physical functioning and health-related quality of life, as well as impaired active participation in community-based physical activity and sports [3,4]. Therefore, the ICF is an important biopsychosocial framework to consider when designing and implementing rehabilitation programs for people with disabilities [5,6]. Hence, evidence suggests that effective rehabilitation interventions for people with ABI should include improvements in all domains [6,7].

Numerous studies have highlighted the positive outcomes of exercise therapy programs for people with ABI. Based on motor learning principles, several systematic reviews have consistently demonstrated the activation of supplementary motor areas and more consistent functional recovery compared to usual care alone [8,9,10,11,12]. In terms of design, multidisciplinary approaches that emphasize the integration of exercise therapy with social leisure activities are considered essential to elicit neuroplastic adaptations that enhance physical recovery [11,13,14,15], and address cognitive and behavioral sequelae following ABI [16,17]. In addition, group-based therapy programs with fewer participants per session have positively affected ABI patients’ quality of life, self-esteem, and social inclusion, as this format encourages and maximizes extensive patient interactions [18,19,20,21].

In terms of context, some studies have proposed exercise programs to ensure a motivational context that facilitates neuroplastic adaptations and behavioral improvements among patients [22,23]. Specifically, an exercise program centered on racket sports is emerging as an accessible therapeutic tool with a strong social component that integrates different body synergies and complex motor strategies, thereby promoting functional performance in both the lower and upper limbs [24].

Despite the noted positive effects of exercise therapy within the ABI population, there remains a noticeable gap in the literature regarding exercise programs that comprehensively address all the domains of the ICF framework. Furthermore, it is frequently observed that these programs do not provide a detailed description of the structure and content of such interventions, thereby limiting their reproducibility [25].

To date, no study has examined the effects of exercise therapy programs based on racket sports for this population. Therefore, the main aim of this study is to design and evaluate the impact of the intervention on health-related quality of life and upper motor control function in ambulant adults with ABI. The secondary aims are to determine the effect of the intervention on functional capacity, mobility, balance, and physical activity participation.

## 2. Materials and Methods

The DISCOVER study protocol was designed in accordance with the Standard Protocol Items: Recommendations for Interventional Trials (SPIRIT) [26] guidelines (Supplementary Table S1). It was registered in the Clinical Trials Registry at clinicaltrials.gov (NCT05358470) and approved by the Regional Ethics Committee for Clinical Research of Madrid (EC 07.22).

### 2.1. Trial Design and Setting

The study protocol describes the methods for a single-blind, randomized, controlled trial with two parallel groups. The trial will compare the effectiveness of a sports-based exercise therapy program in combination with usual care (sET group), versus usual care alone (UC group) in ambulatory adults with ABI. A flowchart of the study design according to the CONSORT guidelines is shown in Figure 1.

The study screening, intervention and assessments will be carried out at a rehabilitation center in Madrid, Spain.

### 2.2. Eligibility and Recruitment

The study population consists of outpatients aged 18 years and over with a confirmed diagnosis of subacute or chronic acquire brain injury. A summary of the eligibility criteria is given in Table 1. Recruitment will take place over a period of 3 months to ensure that the target sample size is achieved. Potential patients from the rehabilitation center database will be invited to participate in the study through site visits and telephone calls. Eligibility will be established through prospective face-to-face interviews and eligible individuals will then be enrolled into the study. Throughout this process, participants will provide a signed written informed consent indicating their understanding of the objectives and requirements of the study.

### 2.3. Allocation and Blinding

After completion of the baseline assessment, independent, centralized, stratified block randomization will be used to allocate participants to either the intervention or the control group. Randomization will be performed using a computer-generated random number sequence, with a 1:1 allocation ratio. The assessors involved in eligibility, pre- and post-intervention assessments, and statistical analysis will be blinded to group allocation throughout the entire study period. Due to the nature of the trial, it is not possible to blind intervention parties, including both participant and program staff, to their group assignments.

### 2.4. Interventions

Exercise therapy program based on racket sports (sET):

Participants in the sET group will participate in an exercise therapy program based on racket sports, combined with their usual care sessions as usual. The program will be delivered over sixteen 60 min sessions, delivered twice a week for 8 weeks. The sessions will be delivered in a group format of four to six participants to optimize social engagement rates.

Session content will be carefully designed based on the motor patterns associated with racket sports, allowing for a progressive and effective transition from specific motor function training to broader sports-related tasks. Exercises are continuously tailored and adapted by a physiotherapist in order to meet the individual needs and functional level of each participant, ensuring accuracy and safety. The Template for Intervention Description and Replication (TIDieR) checklist was used to ensure complete reporting of the intervention (Table 2) [27].

Usual care (UC):

Participants in the UC group will continue to receive their usual care for the duration of the study and will be reassessed. Usual care includes a range of therapies (e.g., occupational therapy, physiotherapy, psychological support) provided by the rehabilitation services within the center. After the post-intervention assessment (T2, 2 months after the intervention), participants in this group will have the opportunity to attend the same program sessions if they wish.

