### 2.8. Sample Size

Based on a review of the literature [35,36], people who undergo an exercise therapy program show improvements such as improved quality of life and functionality. Therefore, the sample size was calculated based on the primary outcomes: SF-36 and FM-UE.

Previous studies have shown that a difference of 12.4 points with an SD of 5 points in the FM-UE score is required to detect the minimum clinically important difference between the two study groups [37,38].

Furthermore, Norman et al. conclude that the threshold for detecting changes in health-related quality of life is approximately 5 points [39]. Taking into account the possible number of subjects we could recruit, the sample size is calculated to detect an improvement of 5 points in the summary components of the SF-36 questionnaire with a standard deviation (SD) of 5 points. The SD value was taken as half that of the general population (SD = 10) because we considered our sample to be more homogeneous. To detect this difference between the groups with a 95% confidence interval and 80% power for a bilateral approach, we would need 16 subjects. If we estimated a 15% attrition rate, the final sample size would be 18 subjects in each group.

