### 2.10. Statistical Methods

The comparability of the study groups will be assessed by the similarity of the distribution of the variables of interest at baseline. The analysis will follow standard methods for randomized controlled trials, using two-group comparisons for all participants on an intention-to-treat basis. The chi-squared test or Fisher´s exact test will be used to compare proportions. Student´s *t*-test will be used to compare means between groups with normally distributed data. The Mann–Whitney test will be used to compare quantitative variables between groups in the case of a non-normal distribution, as determined by the Kolmogorov–Smirnov test. Correlations between quantitative measures will be determined by Spearman’s rho correlation coefficient. Matched pair data analysis is also calculated. In addition, multivariate analysis will be performed using multiple linear regression and logistic regression, depending on the response under consideration. This will allow for adjustment of the effectiveness of the intervention for potential confounders and the identification of other variables associated with each of the outcomes. Statistical significance will be set at ≤0.05. Data will be analyzed using the Statistical Package for the Social Science (SPSS) software, version 27.0 (IBM Corp, Armonk, New York, NY, USA).

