## 3. Discussion

This paper outlines the background and design of a randomized controlled trial that aims to determine the effectiveness of an 8-week exercise therapy program based on sports, combined with usual care, for ambulant adults with ABI, compared to usual care alone.

While previous studies reported positive results from implementing exercise therapy programs centered around sports such as basketball or soccer among people with physical disabilities [40], this study extends the scope of exploration on racket sports, specifically focusing on the ABI population.

A notable strength of this clinical trial lies in the multi-component nature of both the intervention design and assessments: (1) the program encompasses specific neurorehabilitation content alongside sports-based functional exercises that promote interactions and socialization among participants [19,21,40], and (2) the outcome measures involve a range of standardized scales and questionnaires that provide a comprehensive assessment of all the ICF domains [5,6].

As highlighted in earlier research, the proposed sport-based design emphasizes the importance of notably addressing the social domain within ABI rehabilitation, as the focus on the physical domain still predominates in this context. Further studies that integrate sport-based elements into their therapeutic approaches are needed to achieve higher levels of social inclusion within the functional rehabilitation field [9,21,41].

If this program proves effective, it will contribute to clinical practice implications for ABI rehabilitation, offering an evidence-based therapy option that emphasizes the social inclusion perspective and optimally addresses both physical and social recovery. In addition, the results of this study are expected to offer valuable guidance to multidisciplinary teams in achieving optimal levels of health-related quality of life and active lifestyles for their patients.

Finally, it is anticipated that the findings of the trial will be disseminated through peer-reviewed journals and presented at national and international conferences, contributing to broader knowledge and clinical practice in the field of ABI rehabilitation.

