Intervention procedures	sET group: The content of this program is designed to synergize exercise therapy and sports elements. This approach facilitates transitioning from specific motor functional rehabilitation (first eight sessions) to more global skills based on racket sports (final eight sessions). UC group: Usual care encompasses a range of therapies (e.g., occupational therapy, physiotherapy, psychological support) provided by the rehabilitation services within the center. Following the post-intervention assessment, participants from this control group can participate in the same program sessions upon request.
Provider	sET group: The program will be delivered by a physiotherapist with expertise in neurological disorders and adapted physical exercise. UC group: Usual care for this group will be provided by professionals from the rehabilitation center.
Mode of intervention delivery	sET group: Presential, group-based sessions (from four up to six participants) to optimize the rates of social engagement. UC group: Presential, individual sessions.
Setting of intervention	Screening, interventions, and assessments will be conducted at the physiotherapy rooms of a rehabilitation center located in Madrid, Spain.
Dosage	sET group: Participants from this group will receive an 8-week exercise program which consists of sixteen sessions, 1 h session/day for 2 days/week. UC group: This group will continue with their usual care as usual 2 days/week, over 8 weeks and then will be reassessed.
Tailoring	The sessions content will be continuously tailored and adapted by a physiotherapist to meet the individual needs and functional levels of each participant, thereby ensuring precise execution and security.
Modifications	Not applicable.
Fidelity assessment	The therapist responsible for delivering and managing the intervention will conduct a phone follow-up every 2 weeks to monitor the adherence of the sET group to the program. Additionally, this professional will track the progress of participants from the UC group during these follow-up calls.

**Table 3 jcm-12-07068-t003:** Schedule of enrolment, interventions, and assessments from the SPIRIT guidelines.

	Study Period		
	Allocation	Post- Allocation	Completion
TIMEPOINT	T0	T1	T2
*ENROLLMENT:*			
Eligibility screen	X		
Informed Consent	X		
*INTERVENTIONS:*			
Sport-based Exercise Therapy Program + Usual Care			
Usual care			
*ASSESSMENTS:*			
Sociodemographic, anthropometric and comorbidity data		X	

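### One arm is treated in interacting groups of four to six and the other individually, yet the sample size and tests assume independent participants; any positive within-group correlation makes the stated precision and power too favourable

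*Protocol article*

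**What the plan says.** All references are to the protocol article.

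- **Delivery of sET.** Section 2.4: "The sessions will be delivered in a group format of four to six participants to optimize social engagement rates". The dose is given there too: "The program will be delivered over sixteen 60 min sessions, delivered twice a week for 8 weeks".
- **Delivery of usual care.** Table 2, mode of delivery: "UC group: Presential, individual sessions".
- **Intended mechanism.** The Introduction says of small-group therapy that "this format encourages and maximizes extensive patient interactions". The Discussion counts as a strength the "sports-based functional exercises that promote interactions and socialization among participants".
- **Randomization.** Section 2.3 randomizes individuals 1:1.
- **Sample size.** Section 2.8 aims to "detect an improvement of 5 points in the summary components of the SF-36 questionnaire with a standard deviation (SD) of 5 points", two-sided at 5% with 80% power. It reaches 16, then 18 in each group after 15% attrition. For the other primary outcome it cites "a difference of 12.4 points with an SD of 5 points in the FM-UE score".
- **Analysis.** Section 2.10 plans to proceed "using two-group comparisons for all participants on an intention-to-treat basis". It names Student's t-test, Mann–Whitney, chi-squared or Fisher tests, and multiple linear or logistic regression.

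Neither 2.8 nor 2.10 mentions session groups, an ICC, a design effect or a group term.

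**The concern.** This is a partially nested design: participants are randomized individually, then one arm is gathered into groups and the other is not. People who share sessions and peers for up to sixteen hours may finish more alike than people in different groups, and the program is designed to make them interact. If so, the sET mean varies more than individual-level formulas allow, because one unusually good or poor group out of three or four can move it.

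The planned tests count that shared variation as independent individual noise. The standard error of the between-arm difference would then be too small, intervals too narrow, and the 80% power in 2.8 too optimistic. The trial is sized tightly, so there is little slack. Group membership also has to be recorded during delivery; no later analysis plan can use it if it was not kept.

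**Working it through.** **Inputs from the article.** SF-36 difference 5, SD 5; two-sided 5%; power 80%; 16 per arm before and 18 after attrition (2.8); groups of m = 4 to 6 in sET only (2.4, Table 2). The 16 is read as per arm because 2.8 goes on to 18 in each group.

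**Assumed, because not given.** ICC of 0.01, 0.05, 0.10 and 0.20; stable group membership; the same total SD in both arms.

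**1. The plan's own figure.** Under independence, n per arm = 2 × (1.960 + 0.842)² × 5² / 5² = 15.7, so 16. This matches exactly, so no clustering allowance is in it. Power at 16 is 80.7% by this normal approximation (78.1% with the t distribution). FM-UE alone (12.4 / 5 = 2.48 SD) needs 3 per arm, or 4 with the t distribution, so SF-36 drives the size.

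**2. Standard error and power with correlation.** The sET variance is multiplied by DE = 1 + (m − 1) × ICC; the usual care variance is unchanged.

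- SE = √(25 × DE / 16 + 25 / 16)
- Power = Φ(5 / SE − 1.96)
- Example, m = 5 and ICC 0.10: DE = 1.4; SE = √(60 / 16) = 1.936, against √(50 / 16) = 1.768 under independence; power = Φ(2.582 − 1.96) = 73%.

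| ICC | DE in sET (m = 4 to 6) | SE understated by a factor of | Power at 16 per arm | n per arm for 80%, before attrition |
|---|---|---|---|---|
| 0 | 1 | 1 | 81% | 16 |
| 0.01 | 1.03–1.05 | 1.01 | 80% | 16–17 |
| 0.05 | 1.15–1.25 | 1.04–1.06 | 76–78% | 17–18 |
| 0.10 | 1.3–1.5 | 1.07–1.12 | 72–75% | 19–20 |
| 0.20 | 1.6–2.0 | 1.14–1.22 | 64–70% | 21–24 |

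This treats the standard error as known. With it estimated from 3 or 4 groups, power is lower still (step 4).

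**3. Type I error of the planned t-test.** Simulation, 100,000 runs per setting, usual care independent, equal arm sizes, sET group effects averaging zero:

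| sET groups | ICC 0 | 0.01 | 0.05 | 0.10 | 0.20 |
|---|---|---|---|---|---|
| 4, 4, 4, 4 | 5.0% | 5.2% | 5.7% | 6.8% | 8.8% |
| 6, 5, 5 | 4.9% | 5.2% | 6.3% | 7.6% | 10.5% |
| 5, 5, 4, 4 | 5.0% | 5.2% | 6.0% | 7.4% | 9.5% |
| 6, 6, 6 | 4.9% | 5.4% | 6.6% | 7.9% | 11.4% |

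A separate set of 40,000 runs agreed within simulation error; its lowest value at ICC 0.01 was 5.1%.

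**4. What a nested analysis costs.** A partially nested comparison without covariates (between-group mean square for sET, Satterthwaite degrees of freedom, group variance set to zero when its estimate is not positive), 40,000 runs, true difference 5:

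| sET groups | t-test power, ICC 0 | Nested power, ICC 0 | Nested power, ICC 0.10 | Group variance estimated as zero, ICC 0.10 |
|---|---|---|---|---|
| 4, 4, 4, 4 | 78% | 68% | 62% | 43% |
| 6, 5, 5 | 78% | 64% | 55% | 45% |
| 5, 5, 4, 4 | 83% | 74% | 66% | 42% |
| 6, 6, 6 | 83% | 69% | 58% | 44% |

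The loss at ICC 0 is about 10 to 14 points (9 in the 5, 5, 4, 4 layout). Type I error there is 3.2 to 3.5%, so the method is conservative.

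**The case against.** A reader might infer that the standard errors are too small and that type I error exceeds 5%. The article does not support that as a fact. Several points count against it:

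- **No ICC is given.** At 0.01 nothing of practical importance changes.
- **Stable groups are not stated.** The article gives only a session size. If participants mix across the sixteen sessions, the correlation weakens and a single group label is not well defined.
- **Some features point to a low ICC.** Content is tailored to each participant. A physiotherapist delivers the program, which, if it is one person, removes between-therapist variation. The social argument bears mainly on SF-36 and less on FM-UE, a clinician-rated motor scale.
- **The null matters.** With individual randomization, if sET affects nobody, forming groups afterwards does not invalidate the comparison. The inflation in step 3 needs group-specific effects that average zero.
- **Article scope.** A fuller protocol or analysis plan could add a group term.

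The first four stand as limits on certainty and size. The last stands only in part: 2.8 fixes a number that rests on independence, and the analyses that 2.10 names rest on it too.

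A second tempting inference is that the nested model should replace the planned primary analysis. Step 4 argues against imposing that: it costs about 10 to 14 power points even with no clustering, and with 3 or 4 groups it often cannot detect the variance it is meant to model. Nor is it harmless when that variance is estimated as zero: with separate residual variances by arm it then reduces to an ANCOVA with unequal variances, not to ordinary ANCOVA.

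**Conclusion.** The point holds conditionally. Group delivery in one arm, individual delivery in the other, and independence in both the sample size and the named tests are all in the article. For any positive within-group correlation, the standard error of the difference is understated and the 80% power is too favourable. The effect is negligible at ICC 0.01, modest at 0.05, and material from about 0.10: an understatement of the standard error by 7 to 12%, type I error of 7 to 8%, and power of 72 to 75%. These sizes rest on assumed ICCs, stable groups and group effects that average zero.

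The power consequence concerns SF-36, since the FM-UE assumption leaves a wide margin; the interval and type I consequences apply to either outcome to the extent that it is correlated within groups. This is worth correcting, but it is not a flaw that invalidates the trial.

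**What to change.** 1. **Record** the session group of every sET participant, including changes between sessions.
2. **In 2.8**, state that 16 per arm and 80% power assume ICC = 0, and show power over an assumed ICC range such as that in step 2.
3. **In 2.10**, keep the planned individual-level comparison, adjusted for baseline, as primary. Pre-specify as a sensitivity analysis a partially nested mixed model: random session-group effect in sET only, separate residual variance by arm, Satterthwaite or Kenward–Roger degrees of freedom.
4. **Report** the ICC with its interval, and qualify the conclusions if the two analyses disagree.

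The cost is one recorded variable and some wording. The sensitivity analysis will be imprecise: at ICC 0.10 the group variance is estimated as zero in over 40% of runs. A non-significant nested result should therefore be read alongside its interval, not as proof that the primary result is wrong.
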